14. CTCAE grade 3 fatigue, lasting for >7 days
15. CTCAE grade 3 hypertension, hand-foot skin reaction, diarrhea, nausea, and vomiting that are not relieved by symptomatic treatment until the next treatment cycle.
16. CTCAE grade 3 abnormal laboratory examinations that are not relieved by symptomatic treatment until the next treatment cycle.

If one subject experiences toxicity that met the criteria for DLT, the study treatment was interrupted and follow-up was performed as described in the study procedures. Treatment can be discontinued due to any DLT. However, under the investigator and co-sponsor approval, subjects with DLT could receive the next lowest dose level after recovery.

- 1. Efficacy assessment
     1. Primary endpoint
- **Progression-free survival:**

PFS is defined as the time from enrollment to the first time of PD or death from any cause, whichever occurs first.

If the subject did not experience disease progression or death, PFS is defined as the date of the last confirmed progression-free. Subjects who discontinued for reasons other than disease progression (no subsequent tumor imaging assessment) and starting subsequent therapy after the trial were censored at the time of discontinuation or the initiation of subsequent therapy. In cases other than those described above, pre-planned sensitivity analyses will undertake to define PFS based on the date of confirming imaging progression events. New onset other tumor is not considered indicative of PD and is not censored as data.

If the image examination and assessment show PD, the date of PD is not defined as the imaging time of first signs of PD, but the time of definite imaging evidence of PD. If the PD is diagnosed with other clinical examinations, the date of PD is defined as the diagnosis time.

- - 1. Secondary endpoints
- **OS:** OS is defined as the time from enrollment to the date of death due to any cause. For the analysis of OS, data for patients who are alive will be censored for OS at the time of the last follow-up. Data for patients who were lost to follow-up will be censored for OS at the last date they were known to be alive. Censored OS is defined as the time from randomization to censor.
- **1-year PFS rate:** 1-year PFS rate is defined as the percentage of patients who have not progressed or died at 1 year.
- **1-year OS rate:** 1-year OS rate is defined as the percentage of patients who are still alive at 1 year.
- **Duration of response (DOR):** DOR is defined as the time from first documented evidence of complete response (CR) or partial response (PR) until PD or death, whichever occurred first. For the analysis of DOR, data for patients who discontinue study due to due to reasons other than disease progression (without subsequent imaging examinations) or hose who received post-trial treatment will be censored at the time of study discontinuation or the initiation of post-trial treatment. The occurrence of newly developed other tumors is not considered as a PD event, and will be not censored.
- **Disease control rate (DCR):** DCR is defined as the percentage of subjects with PR, CR, or stable disease (SD) lasting for ≥4 weeks.
- **Objective response rate (ORR):** ORR is defined as the percentage of subjects with confirmed tumor volume reduction to pre-specified values and maintenance of minimum time requirements (≥4 weeks), including subjects with a PR or CR. Objective responses are assessed per RECIST v1.1. Subjects must have at least one measurable lesion at baseline. The response was classified as CR, PR, SD, and PD according to RECIST v1.1.
  1. Safety assessment
     1. Safety management

Various management will be taken to ensure the safety of subjects in the study, including strict inclusion and exclusion criteria and close monitoring (hospitalization monitoring, follow-up, and out-of-hospital diary card recording and telephone follow-up).

Safety is analyzed in the safety analysis set (SAS).

- - 1. Adverse events

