**Protocol Synopsis**

| Protocol Title | TQB2450 plus anlotinib in EGFR+ advanced non-small-cell lung cancer patients failed to prior EGFR TKI therapies: a multi-center, single-arm, phase I/II study |
| --- | --- |
| Protocol Number | ALTER-L038 |
| Sponsor | Jiangsu Cancer Hospital |
| Co-sponsor | Chia-tai Tianqing Pharmaceutical Co., Ltd. |
| Study Nature | A phase I/II study |
| Study Population | Patients with EGFR+ advanced non-small-cell lung cancer who failed prior EGFR TKI therapies |
| Objective | Phase I part: To determine the maximum tolerable dose (MTD) of anlotinib and TQB2450.  Phase II part: To evaluate the efficacy and safety in EGFR+ advanced non-small-cell lung cancer patients who failed prior EGFR TKI therapies |
| Study Design | Phase I part: 3+3 dose-escalation study  Patients are treated with anlotinib at 3 levels of 8 mg, 10 mg, and 12mg, and TQB2450 at a fixed dose of 1200 mg. The dose-escalation starts with the combination of 8mg anlotinib and TQB2450. Monitor dose-limiting toxicity (DLT) during one cycle to determine the MTD for patients. MTD is defined as the maximum dose with ≤33% risk of DLT. DLT is defined as drug-related toxicity occurring during the first 21 days of therapy that results in grade 4 hematological toxicity, neutropenia (ANC<1000/μL, fever of ≥38.5℃), grade 2 hepatic or renal dysfunction (lasting >7 days despite symptomatic treatment), and grade 3 or higher non-hematological toxicity (excluding alopecia).  Phase II part: A multi-center, single-arm, phase II study  The eligible patients are treated with anlotinib at the dose of 12 mg plus TQB2450 at the dose of 1200 mg, which is determined in phase I study. All patients were treated until events meeting the termination criteria. The efficacy and safety of anlotinib combined with TQB2450 are further evaluated. |
| Planned Sample Size | Phase I part: 3-18 patients  Phase II part: 54 patients |
| Principal Investigator | [name] |
| Clinical Study Unit | Jiangsu Cancer Hospital |

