Subjects who have received treatment with first or second-generation EGFR TKIs are required to provide a genetic testing report, proving the absence of primary or acquired *T790M* mutations. Subjects who have received treatment with third-generation EGFR TKIs are required to provide a genetic testing report, proving the positivity of EGFR mutations. For subjects with access to tissue samples, it is recommended to prioritize tissue-based *EGFR* mutation testing. Subjects without access to tissue samples may choose blood-based *EGFR* mutation testing using traditional gene testing (such as ddPCR, Arms-PCR, etc.) or high-throughput sequencing. T790M mutation and Exon 20 insertion mutation are key sites for testing.

PD-L1 expression is measured in suitable subjects from sub-centers with testing conditions.The selected subjects should meet the criteria for biopsy, and it is anticipated that sufficient tissue will be obtained for immunohistochemistry. Fresh tissue is divided into two parts, with one directly used for the immunohistochemistry of PD-L1, and the other prepared into a paraffin block for TMB testing.

- 1. Maximum tolerated dose and dose-limiting toxicity

MTD: Toxicity and safety are observed to determine the MTD of anlotinib when combined with TQB2450. MTD is defined as the highest dose when less than 33% of subjects experienced DLT.

DLT: DLT is defined as any one of the following toxicities occurring within the first 21 days of treatment (including events that started in the first cycle but were confirmed in the second cycle), as per NCI CTCAE 5.0.

1. Grade IV hematologic toxicity and following events:
2. ≥ CTCAE grade 3 febrile neutropenia (ANC<1000/ul; body temperature ≥38.5°C)
3. ≥ CTCAE grade 3 neutropenia lasting for >7 days
4. CTCAE grade 3 platelet count decreased lasting for >7 days, with signs of clinically significant bleeding or need for platelet transfusion
5. Grade II or higher liver and kidney dysfunction (lasting for >7 days after symptomatic treatment) and following events:
6. CTCAE grade 2 bilirubin increased, lasting for >7 days
7. ≥ CTCAE grade 3 bilirubin increased
8. CTCAE grade 3 AST or ALT increased, lasting for >7 days
9. CTCAE grade 4 AST or ALT increased
10. Grade III or higher non-hematologic toxicity (except for alopecias) and following events:
11. ≥CTCAE grade 2 pancreatitis
12. Cerebral hemorrhage, ≥grade 2 pulmonary hemorrhage
13. grade 2 abnormal coagulation or bleeding, lasting for >7 days

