**(2)** **Hypertension**

In previous studies, anlotinib is associated with the frequent occurrence of hypertension and the incidence of grade 3 or higher hypertension was 13.61%. During this study, subjects are recommended to monitor blood pressure during treatment. In the event of a hypertensive event, the following managements are recommended:

Grade 1: Pre-hypertension (systolic blood pressure [SBP] 120-139 mmHg or diastolic blood pressure [DBP] 80-89 mmHg); No indication for antihypertensive drugs and blood pressure is monitored.

Grade 2: Stage 1 hypertension (SBP 140-159 mmHg or DBP 90-99g mmHg); Medical intervention is required. For recurrent or persistent (≥24 hours), symptomatic hypertension with >20mmHg SBP increases or >140/90 mmHg increase of previously normal range, monotherapy and blood pressure monitoring are required. Thiazide diuretic, angiotensin-converting enzyme inhibitors (ACEI), angiotensin II receptor blockers (ARB), beta-blocker, or calcium-channel blocker are commonly used.

Grade 3: Stage 2 hypertension (SBP ≥160 mmHg or DBP ≥100 mmHg); Medical intervention is required. Multidrug therapy is required, commonly using a thiazide diuretic combined with an ACEI, beta-blocker, or calcium-channel blocker.

Grade 4: Life-threatening (e.g., malignant hypertension, persistent neurological deficit, hypertensive crisis). Urgent treatments are required.

Hypertension emergencies: SBP >120 mmHg accompanied by acute or progressive target organ damage (e.g., Cerebral infarction, intracranial or subarachnoid hemorrhage, hypertensive encephalopathy, etc.); among them, the progressive or rapidly progressive hypertension based on chronic essential hypertension is the most common (about 40%-50%).

Hypertension urgencies: SBP >120 mmHg with no or minor organ damage.

In case of hypertensive crisis, subjects should discontinue the study treatment and withdraw from the study.

When subjects occur elevated blood pressure during vital sign measurements, a second measurement should be taken after a 15-minute rest. If the elevation is repeated and reaches the grade 2, it can be defined as an AE of hypertension. If the time of improvement from the first occurrence of hypertension to its reappearance is less than 1 week, it is identified as one AE and record the highest level of severity. The start time is defined as the time of the first hypertensive episode, and the end time is defined as the last outcome time of hypertension.

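### Section 6.3 counts every grade 3 or higher non-haematologic toxicity except alopecia as a DLT, then sets persistence conditions on the same grade 3 events, so the 3+3 decision depends on which line is applied

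*Protocol*

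**What the plan says.** Section 6.3 (Maximum tolerated dose and dose-limiting toxicity) opens with "DLT is defined as any one of the following toxicities occurring within the first 21 days of treatment", so meeting one entry is enough. The entries that matter here are:

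- The general non-haematologic line: "Grade III or higher non-hematologic toxicity (except for alopecias) and following events". It carries no duration or refractoriness condition.
- Under that heading: "CTCAE grade 3 fatigue, lasting for >7 days".
- Under that heading: "CTCAE grade 3 hypertension, hand-foot skin reaction, diarrhea, nausea, and vomiting that are not relieved by symptomatic treatment until the next treatment cycle". A further line applies the same unrelieved-until-next-cycle condition to grade 3 laboratory abnormalities.
- Under the separate liver and kidney heading: "CTCAE grade 3 AST or ALT increased, lasting for >7 days".

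The Study Design row of the Protocol Synopsis gives only the unqualified non-haematologic criterion, "grade 3 or higher non-hematological toxicity (excluding alopecia", and none of the specific entries. It also adds a causality condition that the Section 6.3 definition lacks: "DLT is defined as drug-related toxicity occurring during the first 21 days of therapy".

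The Stage 1 rules in Section 6.1 turn entirely on the DLT count. With none in three patients, the dose escalates (or, at 12 mg, becomes the phase II dose). With one in three, three more patients are added and any further DLT fails the level. With two or more in three, the level fails.

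**The concern.** The general line and the specific lines classify the same event differently. Grade 3 hypertension brought under control within days meets the general line on the day it is graded, but does not meet the hypertension line. The same holds for grade 3 fatigue of up to seven days and for grade 3 diarrhoea, nausea, vomiting, hand-foot skin reaction or laboratory changes that resolve before the next cycle. Grade 3 ALT can be read three ways: immediately (general line), after more than seven days (AST/ALT line), or if unrelieved until the next cycle (laboratory line).

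The relatedness wording adds a second split. A disease-related grade 3 event counts on the words of Section 6.3 and not on those of the synopsis.

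The DLT count is the decision variable of phase I, and cohorts are three to six patients. Two investigators applying the text in good faith can reach different phase II doses, and the dose chosen is given to 54 phase II patients.

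**Working it through.** **Which reading does the text support?** Under the non-haematologic heading, the entries for pancreatitis of grade 2 or more, cerebral haemorrhage or pulmonary haemorrhage of grade 2 or more, and prolonged grade 2 coagulation abnormality or bleeding extend the general line to lower grades. Under the haematologic heading, the listed grade 3 events likewise add to grade IV toxicity. In those places the specific entries are additions. Read as additions, the fatigue, hypertension-group and laboratory lines do nothing, because every such event is already a DLT. They have an effect only as exceptions, which the text does not say. The conflict lies in the words and does not depend on how the list is numbered.

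**The plan's own figure.** The phase I size of 3 to 18 reproduces (one cohort of 3; 3 levels × 6 patients = 18) and is not affected.

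**Effect on the decision.** Take two of three patients with grade 3 hypertension relieved before the next cycle and no other DLT:

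| Anlotinib level | General line (2/3 DLTs) | Specific line (0/3 DLTs) |
| --- | --- | --- |
| 8 mg | study terminated | escalate to 10 mg |
| 10 mg | phase II at 8 mg | escalate to 12 mg |
| 12 mg | phase II at 10 mg | phase II at 12 mg |

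One event can be enough: if one of the first three patients has an undisputed DLT, a single disputed event in the next three decides whether the level passes.

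**How often this could matter.** Section 6.5.6.2 (2) says of previous anlotinib studies that "the incidence of grade 3 or higher hypertension was 13.61" per cent. Assume, as an upper end, that this is the cycle 1 risk at every level, that all such events are controllable, and that patients are independent. With p = 0.1361 and q = 1 − p = 0.8639, on the general line:

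- P(at least 1 of 3) = 1 − q³ = 1 − 0.645 = 0.355.
- P(at least 2 of 3) = 3p²q + p³ = 0.051.
- P(exactly 1 of 3) = 3pq² = 0.305.
- P(level fails) = 0.051 + 0.305 × 0.355 = 0.159.

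At half that incidence (p = 0.068), the first and last become 0.190 and 0.047. On the specific line hypertension contributes about 0 in both cases.

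**With other DLTs present.** Let b be the risk of undisputed DLTs, independent of hypertension. On the general line p = 1 − (1 − b)(1 − 0.1361); on the specific line p = b. P(level passes) = q³ + 3pq² × q³. The last column cubes this, assuming equal risk at all three levels.

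| b | Reading | p | One level passes | All three pass |
| --- | --- | --- | --- | --- |
| 0% | specific | 0% | 100% | 100% |
| 0% | general | 13.6% | 84.1% | 59.5% |
| 10% | specific | 10.0% | 90.6% | 74.4% |
| 10% | general | 22.3% | 66.0% | 28.7% |
| 20% | specific | 20.0% | 70.9% | 35.6% |
| 20% | general | 30.9% | 47.6% | 10.8% |

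**The case against.** The strongest reply is that the list never says *only if*. Read literally, any grade 3 or higher non-haematologic event meets the general line, the synopsis agrees, and the later lines are redundant rather than contradictory. That is a possible reading, but it voids three lines that someone wrote for a purpose. Nothing in the text stops an investigator from treating them as exceptions.

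The synopsis also says the 12 mg dose is the one determined in phase I, which suggests escalation is complete and no level was failed. Sections 3.1, 5.5.1 and 5.5.3 still describe the dose by reference to whatever MTD phase I finds, so the trial's stage is unclear. If escalation is complete, the remaining question is whether recorded cycle 1 events would be classified differently under a single rule. The protocol gives no DLT counts to settle it.

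The hypertension figures are a ceiling. The 13.61% comes without dose, population or observation period. It includes grade 4 events, which count as DLTs on either reading, so about 0 on the specific line holds only if all events are grade 3 and controlled. The exclusion of patients with poorly controlled hypertension may lower the rate, and the halved value is arbitrary. These limits stand, but the contradiction does not rest on the figure.

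Two side points are weaker than the main one. AST/ALT has its own heading, so its conflict arises only if the general line also governs events with a dedicated category. On relatedness, Section 6.3 omits a condition rather than stating the opposite, and causality is assessed for every adverse event in any case. Both still leave two possible DLT calls for one event.

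**Conclusion.** The concern holds. The DLT definition gives two answers for the same grade 3 non-haematologic events, no sentence ranks the lines, and the synopsis and Section 6.3 differ on drug-relatedness. Because the 3+3 rules act directly on the DLT count, this is a decision rule that cannot be applied uniquely as written, and it must be fixed.

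The contradiction is textual and needs no assumption. Its size does: if the 13.61% applied to cycle 1 and all events were controllable, hypertension alone would give a 36% chance of at least one DLT in three patients and a 16% chance of failing a level on the general line (19% and 5% at half the incidence), against about 0 on the specific line. Other affected toxicities would add to this. Which criterion is clinically right is not judged here.

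**What to change.** Reconcile the Study Design row of the synopsis with Section 6.3:

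- Give one DLT list in which the general grade 3 or higher line and the specific lines for fatigue, the hypertension group, laboratory abnormalities and AST/ALT cannot both govern the same event. State for each specific line whether it is an exception or an addition.
- State once, identically in both places, whether drug-relatedness is required.
- Re-adjudicate the cycle 1 events already recorded against the single list, and confirm that the phase II dose still follows from the Section 6.1 rules. If escalation is still open, do this before any further DLT call.

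The clinical content of the list is for the investigators and sponsor to decide. The cost is amendment wording plus a review of the cycle 1 events of at most 18 patients.
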